### Data collection

2.4

#### Aim 1a

2.4.1

Data for the validation and computable phenotype study will be collected through retrospective chart review. Trained clinical research coordinators or physicians will review the EHR of patients who had an ICD-10 code for LGS (G40.81x) between January 1, 2016, and December 31, 2022, (as well as a sample without G40.81x, as detailed below) at their respective sites and will record key information reflecting diagnostic criteria for LGS into CLIRINX^1^, a secure web-based clinical research informatics platform designed to support data collection for epilepsy and rare disease clinical research. This information includes seizure history, treatment history (and current medications), etiology/antecedent factors, EEG findings, developmental status/intellectual disability, functional abilities, and neurosurgical interventions. Once data are entered for a given patient in CLIRINX, two pediatric epileptologists, from principal sites different than that of the patient, will independently review the data to classify the patient as having (1) classic LGS, (2) pragmatic LGS, or (3) not LGS. Definitions for each classification are shown in Table 2. If discordant, the file will be automatically sent to a third reviewer ([name]) for adjudication. The LGS classification workflow is shown in Figure 2. A sample of patients without an ICD-10 code for LGS but with a nonspecific ICD-10 code often associated with intractable epilepsy (G40.21^2^, G40.41^3^, G40.80^4^, G40.91^5^) will also be reviewed using the same process for data extraction and central review. New computable phenotypes for LGS will be developed using ICD-10 codes, medication history, and other information available in the EHR. Of note, the International League Against Epilepsy (ILAE) definition published in 2022 came after the development of this study protocol and initiation of this study (36). The retrospective study period is 2016 through 2022, the most recent complete year of data at the time this study was initiated.

**Table 2 tab2:** LGS classifications in Aim 1a.

Classification	Definition
Classic LGS	Meets classic criteria for LGS: Tonic seizures At least one other generalized seizure type Onset of seizures in the first 5 years of life Generalized slow spike-and-wave on EEG (<3 Hz) Cognitive impairment
Pragmatic LGS	Meets pragmatic criteria, as used in randomized trials, for LGS: At least 2 types of generalized seizures including drop seizures; drop seizures include atonic or tonic–clonic Slow spike-and-wave on EEG (<3 Hz) Cognitive impairment
Not LGS	Does not meet either classic or pragmatic criteria for LGS

EEG, electroencephalography; LGS, Lennox–Gastaut syndrome.

**Figure 2 fig2:**
[figure not shown]
LGS classification workflow in Aim 1a. CRCs, clinical research coordinators; EHR, electronic health record; LGS, Lennox–Gastaut syndrome.

Data on emergency healthcare utilization, as well as treatments and covariates, will be extracted from PCORnet® data marts of the 7 high-intensity sites. The data types include demographics, diagnoses and conditions, encounters, procedures, prescriptions, medication administrations, healthcare providers, and deaths. Seizure-related emergency healthcare utilization will be defined as the frequency per year of seizure-related ED visits and seizure-related inpatient admissions in the 2 years after intervention (surgery or medical), with adjustment for the rate during the year before intervention. A secondary analysis will be done for 1 year after intervention as well. The index date of the intervention will be defined between January 1, 2016, and December 31, 2021, as that of the first relevant surgery or (if there was no surgery) that of the first exposure to a third anti-seizure medication, with at least one of the three being among the seven LGS-approved medications listed above. To the extent possible, we will also control for dietary therapy as a variable collected by chart review and accessible by codes. We also will analyze all emergency healthcare visits and inpatient visits (with or without seizure diagnosis codes) and the subset for which there is a diagnosis of fracture, head trauma, lacerations/avulsions/contusions, burns, aspiration, aspiration pneumonia, or near drowning (37), as an expanded seizure-related definition. Subset analysis will be done on data from 2020 and 2021, the years of the COVID-19 pandemic (38).

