## Introduction

1

Lennox–Gastaut Syndrome (LGS) is a severe developmental epileptic encephalopathy that affects an estimated 48,000 children and adults in the United States (US) (1). LGS is characterized by multiple seizure types, life-long treatment resistant seizures, developmental delay, cognitive and behavioral impairments, and early death (2–4). The onset of seizures is typically in the first 2 years of life, but the syndrome is often not fully recognizable until children are 3 to 5 years old (2, 5). Individuals with LGS have multiple types of seizures including tonic–clonic, tonic, and atonic seizures (2). Prolonged seizures are common and require the use of rescue medications, emergency department (ED) visits, and unplanned hospital admissions (6, 7).

LGS, although rare, accounts for a disproportionate amount of healthcare utilization and expenditures. It accounts for up to 10% of all childhood-onset epilepsies and 1–2% of all epilepsies; however, it represents one-fifth or more of treatment resistant pediatric epilepsy (2, 8–10). Among children and adults, expenditures are two or more times greater in association with LGS than with other forms of epilepsy (11), and all-cause mortality in young people with LGS is ten times that in the general population (3). In a survey about living with LGS, 75% of parents reported that their child experienced seizures every day in the prior week, 30% reported going to an ED at least once in the past 6 months, and 51% reported using rescue medication to stop a seizure in the past 6 months (7). In addition to the burdens created by seizures, people with LGS have a profound level of cognitive and physical impairment. A caregiver-driven survey of young people with severe epilepsies found that in the subgroup with LGS, 42% did not walk independently, 25% did not have functional hand grasp, 42% were entirely dependent on someone else for feeding, 55% did not effectively communicate, and 50% were nonverbal (4). This degree of impairment further increases medical burden and financial stress with hidden costs of care, and significantly impacts the quality of life of patients with LGS and their families (12, 13).

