### Study aims

2.1

Aim 1: Determine the effect of epilepsy surgery and LGS-approved anti-seizure medications on two key clinical outcomes in children with LGS.

a. Compare the effectiveness of the addition of surgeries versus the addition of another medication for reducing seizure-related emergency healthcare utilization.

b. Compare the effectiveness of these two pathways and of early versus later use of surgery versus medications on measures of children’s expressive communication, behavior, and quality of life.

Aim 2: For individuals with LGS, describe real-world utilization of these treatments across multiple centers in the US, and identify variability including disparities that may currently pose challenges and barriers to ensuring optimum access to and use of appropriate therapies.

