The primary analyses will compare epilepsy surgery (CC or VNS, CC alone, VNS alone) to the addition of another LGS-approved medication. We also will compare CC to VNS. While CC and VNS are the most common surgeries, we will also explore all epilepsy surgeries including cranial epilepsy surgery, CC, VNS, DBS, and RNS to addition of another LGS-approved medication, to understand VNS and CC in the spectrum of care. We will use a generalized linear mixed model with Poisson distribution and log link to compare the frequency of ED visits and inpatient admissions in the 6 months post-intervention. To guard against any potential biases in the selection of the type of surgical therapy or of surgery versus medication that might arise due to medical complexity, we will employ inverse probability of treatment weighting (IPTW), which uses the propensity score/conditional probability to balance baseline patient characteristics across different treatment groups. Treatment selection will be modeled with a logistic regression using information available at the time the decision is made like age, sex, pediatric complex chronic conditions (PCCC) (39), and anti-seizure medication use. The inverse of the resulting probability will be used to weight each individual in regression models for the outcomes. PCCC scores, reflecting medical complexity, will be calculated from existing data provided by each site. Based on our knowledge of and experience with LGS and its treatment, we do not expect large differences between the patients receiving the different types of therapies. We will describe what the differences are that appear to influence the selective use of these different therapies.

A random site effect will account for clustering within sites. Robust standard errors will be used to control for mild violation of distributional assumptions. In the case of severe violations, a Negative Binomial or zero-inflated Poisson model may also be considered. We will report the conditional rate ratios that estimate the expected rates of ED visits and separate hospitalizations in the surgery arm compared to the medication arm for the 1-year and 2-year periods following intervention. Additionally, a combined variable representing overall emergency healthcare utilization, including both ED visits and inpatient admissions, will be considered.

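### The Aim 1a emergency outcome does not exclude planned seizure-related admissions, which can distort the surgery-versus-medication comparison in both the baseline and follow-up windows

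*Protocol article*

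**What the plan says.** The stated target is emergency care. Section 2.1 compares the two pathways "for reducing seizure-related emergency healthcare utilization". The Introduction describes the burden as "emergency department (ED) visits, and unplanned hospital admissions", and the Discussion paragraph of the abstract also names emergency care for seizures as the outcome that families value.

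The operational definition is in Section 2.4.1 (Data collection, Aim 1a): "Seizure-related emergency healthcare utilization will be defined as the frequency per year of seizure-related ED visits and seizure-related inpatient admissions". The window is the 2 years after intervention, with 1 year as a secondary analysis, "with adjustment for the rate during the year before intervention". The definition does not limit admissions to unplanned, urgent or ED-origin stays. Sections 2.2.1 and 2.6.1 also refer to inpatient admissions without that limit. Section 2.6.1 adds that "a combined variable representing overall emergency healthcare utilization, including both ED visits and inpatient admissions" will be considered.

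The index date is defined "as that of the first relevant surgery or (if there was no surgery) that of the first exposure to a third anti-seizure medication". For a surgical patient, follow-up therefore begins at the operation, and the covariate year is the year leading up to it.

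**The concern.** The label and the aim describe emergency care, while the definition describes any seizure-related inpatient stay. The difference consists of planned stays: pre-surgical evaluation, procedure and device stays, and possibly the index stay. In patients with epilepsy these would ordinarily carry an epilepsy diagnosis code. Starting a third medication creates no comparable procedure stay, so planned stays are likely to be more common in the surgery arm.

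Planned stays can enter the count in two places, with opposite effects. After index they add events to the surgery arm and make surgery look worse. In the year before index they raise the surgery arm's baseline rate. The baseline adjustment then credits surgery with a fall that reflects only the end of the work-up.

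The surgery-versus-medication rate ratio for hospitalizations could then show or hide a difference unrelated to emergency care. The ratios of CC and VNS to each other are exposed in the same way if their planned stays differ.

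**Working it through.** **Is the planned stay removed anywhere?** I compared the definition with each analysis step in the article.

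- The further analyses in Section 2.4.1 either widen the count to all visits, with or without seizure codes, or add a set of injury and aspiration diagnoses. Neither replaces the primary count.
- The inverse probability weights in Section 2.6.1 use variables such as age, sex, complex chronic conditions and anti-seizure medication use. Weighting balances patients; it does not correct an outcome count that treatment itself inflates.
- Robust standard errors and the random site effect address variance and clustering, not this bias.

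**Inputs for an illustration.** The article gives no event rate, effect size or power figure for Aim 1a, so there is no stated figure to reproduce. Its only background figure is in the Introduction: 30% of surveyed parents reported at least one ED visit in 6 months. If visits are Poisson, the rate is −ln(1 − 0.30)/0.5 = 0.713 per year. This covers ED visits only, so I also show 1.5 and 3.0 per year. The number of planned stays is an assumption. The true rate ratio (RR) is set to 1. About one-third of patients are in the surgery arm, as Section 2.5 expects.

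**Step 1: planned stays after index, unadjusted.** With p planned stays per surgical patient, background rate r per year and window T years, the spurious RR is 1 + p/(r × T). For p = 1, r = 0.713, T = 2: 1 + 1/1.427 = 1.70.

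| r per year | p | 6 months | 1 year | 2 years |
|---|---|---|---|---|
| 0.713 | 0.25 | 1.70 | 1.35 | 1.18 |
| 0.713 | 1 | 3.80 | 2.40 | 1.70 |
| 3.0 | 1 | 1.67 | 1.33 | 1.17 |

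Section 2.6.1 names a 6-month window as well as 1 and 2 years; the shorter windows are the more sensitive.

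**Step 2: adjusted for the baseline year.** A Poisson regression was simulated with 60,000 patients and gamma-distributed individual rates (shape 1). Planned stays were Poisson with the mean shown. The baseline count entered either as it stands or as log(count + 0.5), and the ranges span the two codings. Site effects and weights were not simulated. Two-year window:

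| Mean planned stays (before, after index) | r = 0.713 | r = 1.5 | r = 3.0 |
|---|---|---|---|
| 0, 0 | 1.00–1.01 | 1.00–1.01 | 0.98–0.99 |
| 1, 0 | 0.65–0.70 | 0.70–0.77 | 0.78–0.86 |
| 0, 1 | 1.68 | 1.33–1.35 | 1.17–1.18 |
| 1, 1 | 1.18–1.26 | 0.98–1.08 | 0.94–1.04 |
| 2, 1 | 0.92–1.04 | 0.76–0.87 | 0.77–0.90 |

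In the 1-year window, one stay in each period cancels less well: 1.76–1.88 at r = 0.713, 1.24–1.36 at 1.5 and 1.06–1.15 at 3.0. With no planned stays counted, the ratio is 0.98–1.02 in every scenario for both windows, so the artefact comes from the planned stays alone.

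**The case against.** The source is a journal article. Code lists, admission-type filters and the handling of the index stay are commonly left to a full protocol or analysis plan, and one not shown here could exclude elective stays. The construct is called emergency use throughout, and the article does not say which diagnosis position makes a stay seizure-related. That it is set by diagnosis code is an inference from the contrast with the all-visit analysis. This limits how firmly one can say what will be counted. It does not remove the point: the article fixes a definition, and that definition is wider than its stated aim.

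A reader might infer several stronger claims that the article does not support:

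- **That the operation stay certainly counts.** Events are counted after intervention and the index is the surgery date. The article does not say how a stay in progress at index is treated.
- **That the combined variable counts an ED visit and its resulting admission twice.** Section 2.6.1 gives no counting rule and says only that the variable will be considered.
- **That planned stays fall almost only on surgical patients.** A higher frequency is likely, but no frequency or split by arm is given, and medication patients may also have elective monitoring stays.
- **That the bias exceeds any plausible treatment effect, or has a known direction.** No effect size is stated to compare with. The Step 1 ratios ignore the baseline adjustment. Step 2 shows that the two biases oppose each other and, over 2 years at the higher background rates, nearly cancel when there is one planned stay in each period.

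ED visits are also to be reported separately from hospitalizations, and that part is largely unaffected.

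**Conclusion.** The point stands as a mismatch between aim and definition. Aim 1a targets emergency utilization, but its inpatient component as defined admits planned seizure-related stays, in the baseline year and in follow-up, and no analysis described in the article takes them out. They are likely to be more common in the surgery arm.

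The net sign and size of the bias are unknown. With a true RR of 1, the two-year adjusted ratios illustrated above run from 0.65 to 1.68, depending on when the planned stays fall and on the background rate. These figures rest on assumed numbers of planned stays, on a background rate taken from an ED survey figure under a Poisson assumption, and on equal background rates in the two arms. They show that the definition can create or mask a difference in hospitalizations, not that it will.

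**What to change.** Amend the outcome definition in Section 2.4.1 and carry it through Sections 2.2.1 and 2.6.1:

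1. Define the primary inpatient component as seizure-related admissions through the ED or coded urgent or emergent, in the baseline and follow-up windows and in both arms.
2. Exclude planned evaluation and procedure stays from both windows, using procedure codes where admission type is poorly coded.
3. Start counting at discharge from any inpatient stay in progress at index, in both arms.
4. If the combined variable is used, count an ED visit and its resulting admission as one episode.
5. Keep the all-admission count as a secondary analysis, so that the effect of the restriction is visible.

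The cost is a change of wording and a filter. Section 2.4.1 already lists encounters and procedures among the extracted data, but it does not say that admission type is among the fields, so this needs checking at each site. The downside is some misclassification where admission type is poorly coded or not available in the data marts. If an analysis plan already holds such an exclusion, the definition in the article should be aligned with it.

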### Inclusion and exclusion criteria

2.3

Although children in many research studies are defined as <18 or <21 years of age, in practice, children with severe epilepsies such as LGS often remain with their pediatric providers well into their third decade of life, because of severe disability, and may continue to have coverage up to age 26 through their parents’ health insurance plans. Patients in the cohort will have been less-than-or-equal-to 26 years old at the beginning of the study period.

Inclusion and exclusion criteria for Aims 1a, 1b, and 2 are shown in Table 1.

**Table 1 tab1:** Study inclusion and exclusion criteria.

Aims	Inclusion criteria	Exclusion criteria
Aim 1a	Patient has a validated diagnosis of LGS or meets one of the LGS computable phenotype definitions the study evaluated Index treatment occurred between 2016 and 2021: first epilepsy surgery or initiation of additional LGS-approved medication Patient received neurological care at a study site at least 1 year before intervention and 2 years after intervention at the site	Patient does not meet minimum follow up criteria for neurological care at the study site
Aim 1b	Patient has a validated diagnosis of LGS Patient is currently being treated at a study site Caregiver can participate in English or Spanish	
Aim 2	Computable phenotype for LGS based on Aim 1a	

LGS, Lennox–Gastaut syndrome.

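### Aim 1a's index rule admits patients to the medication arm only if they have no later surgery, starts the two arms' clocks at different treatment stages, and conflicts with the stated comparator

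*Protocol article*

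**What the plan says.** The protocol article describes the medication index in three places.

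- **Section 2.4.1 (Aim 1a data collection, after Figure 2):** the index date falls "between January 1, 2016, and December 31, 2021" and is "that of the first relevant surgery or (if there was no surgery) that of the first exposure to a third anti-seizure medication". At least one of the three drugs must be among the seven LGS-approved ones; it need not be the third.
- **Table 1 (Section 2.3):** the index treatment is "first epilepsy surgery or initiation of additional LGS-approved medication". There is no third-drug anchor and no condition about surgery.
- **Section 2.6.1:** the primary analyses compare surgery "to the addition of another LGS-approved medication".

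Eligibility also requires: "Patient received neurological care at a study site at least 1 year before intervention and 2 years after intervention at the site".

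The planned safeguards are an outcome comparison "with adjustment for the rate during the year before intervention" (Section 2.4.1) and inverse probability of treatment weighting (Section 2.6.1). The weights use "information available at the time the decision is made like age, sex, pediatric complex chronic conditions (PCCC) (39), and anti-seizure medication use". Section 2.6.1 introduces weighting because medical complexity may drive treatment choice, but adds that large differences between groups are not expected. Section 3.4 lists staggered cohort entry as a source of selection bias and does not mention the index rule.

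**The concern.** In a cohort comparison, a patient's arm should be fixed by what is known and started at time zero. Here the medication arm is defined by a future non-event. Patients whose course after the third drug leads to surgery leave no third-drug follow-up in the medication arm. If those tend to be the patients doing badly, the medication arm is left with the better courses.

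The two clocks also start at different stages. Medication patients all start at drug three, and surgical patients start wherever in their drug history surgery falls. On the plain reading, the calendar window widens this gap. A patient whose third drug came before 2016 has no medication index date, yet enters as surgical if operated on within the window.

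This rule sets the arms and time zero for the primary comparison of Aim 1a, which is meant to inform families choosing between surgery and another drug.

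**Working it through.** **1. Reading the rule on one patient.** A child starts a third drug in 2017 and has surgery in 2019.

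- Under Section 2.4.1 the index is 2019, in the surgery arm, and 2017–2019 contributes nothing to the medication arm.
- Without the 2019 surgery, the same child is indexed in 2017 in the medication arm.
- The arm at 2017 is therefore decided by an event in 2019.
- The text does not say whether no surgery means ever, within the study period or within follow-up. Each reading looks ahead, to a different extent.

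**2. Reach of the safeguards.** The weights use information available at the decision, and later surgery is not such information. The prior-year rate is also measured before time zero. Neither can bring back patients removed for a later event. Stage is different: age and drug use are baseline variables and can be adjusted for, provided the arms overlap.

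**3. Definition.** Under Section 2.4.1 the index drug may be one not approved for LGS, if one of the earlier two was approved. Table 1 and Section 2.6.1 require the added drug itself to be LGS-approved. The two definitions give different cohorts and index dates.

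**4. Illustrative size.** The article gives no event rate, effect size or power for Aim 1a, so there is no figure to reproduce.

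*Design taken from the article:* the index rule, 1 year before and 2 years after index, a Poisson model with log link, and prior-year-rate adjustment.

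*Assumed, not from the article:* underlying rate centred on 1 event per year; between-patient SD 0.5; fluctuating log severity with SD 0.7 and monthly correlation 0.97; surgery possible after the third drug. The surgery hazard is multiplied by exp(β × current log severity). Weights use age only. The surgery share came out at about 34–41%; Section 2.5 expects about one-third, possibly for Aim 1b only.

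The true rate ratio is 1. Results are means of 8 replicates:

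| Rule | Analysis | β = 0 | β = 0.5 | β = 1.0 |
|---|---|---|---|---|
| As written | crude | 1.02 | 1.39 | 1.81 |
| As written | prior-year rate adjusted | 1.02 | 1.21 | 1.45 |
| As written | age weights + prior-year rate | 1.03 | 1.29 | 1.57 |
| Look-ahead removed | prior-year rate adjusted | 1.02 | 1.15 | 1.28 |
| Look-ahead removed, stage aligned | prior-year rate adjusted | 1.02 | 1.12 | 1.20 |

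Share of the log ratio remaining after both corrections:

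- β = 0.5: ln 1.12 / ln 1.21 = 0.113 / 0.191 = 59%
- β = 1.0: ln 1.20 / ln 1.45 = 0.182 / 0.372 = 49%

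So the index rule accounts for roughly 40–50% of the distortion in these runs. The remainder is confounding by indication.

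With faster-fluctuating burden (monthly correlation 0.90, single runs), the rule as written gave 1.13 and 1.34 with prior-rate adjustment, and 1.20 and 1.47 with age weights added.

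**5. The mechanism in the counts** (single run, β = 1.0, correlation 0.97). The look-ahead cuts the medication arm from 12,457 to 9,447, a loss of 3,010 / 12,457 = 24%. Its prior-year rate falls from 1.40 to 1.24 events per year.

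**6. Stage gap** (single run, n = 40,000, β = 0.5). Surgical patients were indexed 7.2 years after entry at 5.8 drugs on average, and medication patients at 3.7 years and exactly 3 drugs. Only 19% of surgical patients were at drug three, so overlap on drug count is poor.

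**7. Direction.** With rates falling 5% a year since onset and no severity selection, the rule gave 0.83 crude, 0.89 after prior-rate adjustment and 1.00 once age was weighted.

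**The case against.** The strongest reply is that the numbers come from assumptions and the plan already adjusts. Much of that stands.

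- **Bias is conditional.** A reader might infer that the rate ratio must be biased, and biased against surgery. The documents do not support this. The ratio is about 1.0 when surgery is unrelated to burden, and can fall below 1 when rates decline with time since onset.
- **The fix is not a cure.** A reader might expect correct time zeros to bring a null comparison back to 1.00. A separate simulation did show this: 1.15–1.50 under the rule and 0.99–1.01 in risk sets. But it made surgery depend on the prior-year count, the same variable it adjusted for, and it left out the planned weighting. When selection acts on underlying severity, 1.12–1.20 remains.
- **Stage imbalance is partly adjustable.** Age weighting removed it in the falling-rate case. It did not help when surgery followed severity.
- **Timing of LGS.** The Introduction says "the syndrome is often not fully recognizable until children are 3 to 5 years old", so a reader might infer that patients are indexed before they have LGS. The article gives no age at third drug, and how diagnosis is dated against index is detail that a condensed article may leave to the full protocol. This is not part of the finding.
- **The definition mismatch** is real but separate, and lends no weight to the bias figures.

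None of this answers the look-ahead, which is explicit in the rule.

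**Conclusion.** The finding holds in limited form. By its wording, the Aim 1a index rule makes medication-arm membership depend on later surgery, and it anchors medication at drug three with no matching anchor for surgery. Where surgery is chosen partly on burden or prognosis, the rate ratio is biased. Section 2.6.1 itself anticipates selection by medical complexity, so that condition is plausible. The look-ahead cannot be repaired by the planned weighting or prior-rate adjustment. The stage imbalance can be repaired only in part, with poor overlap if drug count is used.

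Neither size nor direction can be derived from the documents. On the base assumptions above, adjusted null ratios were about 1.2–1.6 when surgery followed burden and about 1.0 when it did not, and the index rule explained only part of the excess. The conflict between Section 2.4.1 and both Table 1 and Section 2.6.1 over the index drug needs no assumption and must be reconciled in any case.

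**What to change.** 1. Assign the arm only on the treatment started at time zero, and delete the no-surgery condition from Section 2.4.1.
2. In the primary analysis, keep medication starters who later have surgery in the medication arm. As a sensitivity analysis, censor them at surgery and apply censoring weights.
3. Align time zero between arms by adjusting, matching or stratifying on number of prior drugs and age, and report overlap on both.
4. Reconcile the medication-index definition in Section 2.4.1 with Table 1 and Section 2.6.1, so that one definition governs eligibility, index date and comparator.
5. State that residual confounding by indication is expected after these changes.

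**Cost.** This is mainly wording and programming on existing records. Some index dates change. Some patients may contribute to both arms, so standard errors must be clustered by patient. Fine strata may be sparse: Section 2.5 reports an average of just over 200 patients at each of 7 sites, so about 7 × 200 = 1,400 before validation and the care-duration criteria. Covariate adjustment may be needed in place of exact joint strata.

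### Aim 1a's medication index date is worded more widely than its comparator, so an acute dose during an emergency encounter can set time zero

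*Protocol article*

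**What the plan says.** All references are to the protocol article.

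- **Section 2.4.1 (Data collection, Aim 1a), index date.** The index is the first relevant surgery or, if there was none, "that of the first exposure to a third anti-seizure medication", "with at least one of the three being among the seven LGS-approved medications listed above".
- **Section 2.4.1, data.** Utilization, treatments and covariates come from the data marts. The listed types include "encounters, procedures, prescriptions, medication administrations, healthcare providers, and deaths". The text does not say which of them establishes exposure.
- **Section 2.4.1, outcome.** The outcome is the yearly frequency of seizure-related ED visits and admissions over two years from the intervention, "with adjustment for the rate during the year before intervention".
- **Table 1 (section 2.3).** The index treatment for Aim 1a is "first epilepsy surgery or initiation of additional LGS-approved medication".
- **Section 2.6.1 (Data analysis, Aim 1a).** The comparator for surgery is again the adding of a further LGS-approved drug.
- **Introduction.** "Prolonged seizures are common and require the use of rescue medications, emergency department (ED) visits, and unplanned hospital admissions".

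**The concern.** The question for families is whether to operate or to add a drug, so time zero in the medication arm should be the day a drug was added to ongoing treatment. The section 2.4.1 rule can pick a different day. Take a child on two anti-seizure drugs, one of them LGS-approved, who is given a different anti-seizure drug once in the ED for a prolonged seizure. On the literal rule that child has had a first exposure to a third drug and enters the medication arm that day, even if nothing was added afterwards.

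Two things are at stake. First, time zero can be tied to the kind of event that Aim 1a counts as its outcome. A surgical index is dated by a procedure, so a seizure emergency does not trigger it in the same way. Second, children who never followed the medication pathway can be analysed as if they had.

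The planned safeguards do not remove either problem. The weighting in section 2.6.1 uses examples such as age, sex, medical complexity and anti-seizure medication use, which balance patients but do not move a misplaced index date. The prior-year adjustment changes the sign of the distortion if the encounter falls before index.

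**Working it through.** The document gives no figure on this point to reproduce. The check compares the wordings and then illustrates size under stated assumptions.

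**Step 1: the rules side by side.** Section 2.4.1 differs from Table 1 and section 2.6.1 in two respects.
- *Which drug.* In 2.4.1 the third drug may be any anti-seizure medication, provided one of the three is LGS-approved. In Table 1 and 2.6.1 the added drug is itself LGS-approved.
- *What counts.* In 2.4.1 it is exposure. In Table 1 and 2.6.1 it is initiation or addition.

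The two rules can select different patients and different dates.

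**Step 2: inputs for the illustration.**
- Event rate: 1 seizure-related ED visit or admission per year (assumed).
- f: share of the medication arm whose index is an acute encounter, 10% to 40% (assumed; the document gives no value).
- True surgery-to-medication rate ratio: 1.00.
- No index encounter is counted in the surgery arm.

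**Step 3: encounter counted after index.** With L the expected count in the window, each affected patient gains one event. The medication arm averages L + f and the apparent null ratio is L/(L + f).
- Two years, L = 2: f = 0.10 gives 2/2.10 = 0.95; f = 0.40 gives 2/2.40 = 0.83.
- Six months, L = 0.5: 0.5/0.60 = 0.83; 0.5/0.90 = 0.56. This window matters because the model sentence in section 2.6.1 names six months, while section 2.4.1 names two years with one year as secondary.

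**Step 4: another event rate.** The survey cited in the Introduction reports 30% with an ED visit in six months. Under a Poisson assumption the rate is −ln(1 − 0.30) = 0.357 per six months, or 4 × 0.357 = 1.427 per two years.
- f = 0.10: 1.427/1.527 = 0.93.
- f = 0.40: 1.427/1.827 = 0.78.

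This uses the survey only for an ED rate. It says nothing about f.

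**Step 5: encounter counted in the prior year.** At 1 event per year, an affected patient's baseline rises from 1 to 2, and the arm mean from 1 to 1 + f, that is 1.10 to 1.40. Adjustment then makes the medication arm look worse at the start than it was, which tends to favour medication. Converting this to a rate ratio needs the baseline coefficient, which the document does not give.

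**Step 6: encounter counted in neither.** The mechanical term is zero and the null ratio stays at 1.00. The misclassification of children with no added drug remains.

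**The case against.** The strongest reply is that the article, read as a whole, means started add-on therapy. The Introduction names rescue medication separately from the anti-seizure treatment pathway, Table 1 and section 2.6.1 speak of initiation and addition, and section 2.4.3 describes the Aim 2 drug data as prescriptions. Drug code lists and same-day rules are commonly left to a full protocol or SAP, so their absence is no finding. This carries weight, but section 2.4.1 is not silent. It states a rule, and an analyst who programs that rule as written obtains a wider comparator than Table 1 describes.

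A reader might also infer four stronger claims, which the document does not support:
- *Administrations define exposure.* They are listed among the extracted data types and no more. That they could qualify is an inference.
- *The index event is itself the outcome.* Events are counted after the intervention, and the handling of an encounter on the index date is open. The index can coincide with an outcome event; it is not stated to be one.
- *Only the medication arm is affected.* A surgical admission could also be counted, notably in the planned analysis of all inpatient visits regardless of seizure codes.
- *The Introduction shows f to be large.* The survey states that "51% reported using rescue medication to stop a seizure in the past 6 months" and that 30% went to an ED. These are prevalences in people living with LGS. They do not estimate the share of first third-drug exposures that were acute doses. A rescue drug used earlier might already count among the three.

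**Conclusion.** The point holds as a defect in a stated rule. Section 2.4.1 fixes a medication index that is wider than the comparator in Table 1 and section 2.6.1, and as worded it allows an acute dose in an emergency encounter to start follow-up. It can therefore misdate the comparator and admit children to whom no drug was added.

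Neither size nor direction is established. The two-year range of 0.95 to 0.83 assumes 1 event per year, f of 10% to 40%, counting after index, and nothing counted at index in the surgery arm. If the encounter falls in the baseline year, the adjusted bias tends the other way. The change should be made before the cohort is built; confidence in its practical effect is moderate because f is unknown.

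**What to change.** - **Reconcile** section 2.4.1 with Table 1 and section 2.6.1, including whether the third drug must itself be LGS-approved. The investigators should settle which is meant; the passages must then agree.
- **Index date.** For the cohort definition, use the first outpatient or discharge prescription of the added drug. Rescue formulations, and administrations confined to an ED or inpatient encounter, then neither count toward the three drugs nor set the date. This is a data definition and implies nothing about treatment.
- **Index encounter.** In both arms, exclude it (medication start or surgical admission) from the outcome count and from the prior-year rate, and start the count after discharge.
- **No second-prescription requirement.** That would condition on post-index information in the medication arm only.
- **One sensitivity analysis** excluding medication-arm patients whose index falls within 7 days of a seizure-related encounter.

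The cost is a change to the cohort code and one extra run on data types already listed for extraction. The downside is small: some patients lose their medication index or receive a later one, and a later date may fall outside the 2016 to 2021 index window or leave less than the two years of follow-up that Table 1 requires.
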